### Randomization

2.4

Eligible participants will be randomly assigned in a 1:1:1 ratio to the opposing needling plus electroacupuncture (OE) group, sham opposing needling plus electroacupuncture (SE) group, or electroacupuncture alone (EA) group, according to the order of enrollment. The randomization sequence will be generated by an independent third party not involved in this study using SAS 9.4, with a stratified randomization method; the stratification factor is study center, and the block size is 6. Group allocation will be concealed in sequentially numbered, opaque, sealed envelopes. The envelopes will be opened by the acupuncturist immediately before the first treatment to determine group assignment.

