#### Recruitment

2.2.1

Participants will be recruited from the outpatient clinic of the Rehabilitation Department at Thirteenth People’s Hospital of Chongqing and the Rehabilitation Department at Chengdu Pidu District Traditional Chinese Medicine Hospital, as well as through offline recruitment posters and online social media platforms.

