### Blinding

2.5

Participants, outcome assessors, and statisticians will be blinded to group allocation throughout the study. To maintain blinding, the three groups will be referred to as the OE group, SE group, and EA group, respectively. Due to the particularity of acupuncture, acupuncturists will not be blinded. Acupuncture treatments, outcome assessments, and statistical analyses will be conducted independently by different members of the research team.

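### The fixed, published block size of 6, with unblinded acupuncturists opening the envelopes, lets anyone who knows a centre's past allocations predict many later ones

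*Protocol article*

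**What the plan says.** Section 2.4 (Randomization) of the protocol article says that "Eligible participants will be randomly assigned in a 1:1:1 ratio" and that "the stratification factor is study center, and the block size is 6". Each block within a centre therefore holds 2 OE, 2 SE and 2 EA. An independent third party generates the sequence in SAS. On concealment: "Group allocation will be concealed in sequentially numbered, opaque, sealed envelopes". On opening: "The envelopes will be opened by the acupuncturist immediately before the first treatment to determine group assignment". Assignment follows the order of enrolment.

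Section 2.5 (Blinding) says: "Due to the particularity of acupuncture, acupuncturists will not be blinded". It assigns treatment, outcome assessment and statistical analysis to different team members. Enrolment and the eligibility decision are not in that list.

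Section 2.2.1 (Recruitment) says: "Participants will be recruited from the outpatient clinic of the Rehabilitation Department" at each hospital. It adds posters and online social media as further sources. It does not say who screens.

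**The concern.** Opaque sealed envelopes hide the next assignment from inspection. They do not stop anyone inferring it from past assignments when every block has the same known size. The people who see past assignments here are the acupuncturists, who open the envelopes and deliver visibly different treatments.

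If such a prediction reaches the person who judges eligibility or books the first treatment, a borderline patient can be held back, brought forward or declined according to the arm expected next. The primary outcome is patient-reported, the planned size is 36 per arm, and the listed covariates (age, BMI, disease duration) would not fully capture prognosis altered in this way. Blinding participants and assessors cannot repair groups that already differ at entry.

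**Working it through.** The article gives no predictability figure, so there is none to reproduce.

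**Inputs from the article:** block size 6, ratio 1:1:1, stratification by centre (two centres), total 108 (section 2.3).

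**1. Full knowledge of the current block.** A 2/2/2 block has 6!/(2!·2!·2!) = 90 orders, all equally likely. By position:

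| Position | Certain | At least one arm ruled out | Best guess right |
|---|---|---|---|
| 1 | 0 | 0 | 1/3 |
| 2 | 0 | 0 | 2/5 |
| 3 | 0 | 1/5 | 1/2 |
| 4 | 0 | 3/5 | 8/15 |
| 5 | 1/5 | 1 | 3/5 |
| 6 | 1 | 1 | 1 |
| Sum | 6/5 | 14/5 | 101/30 |
| Sum ÷ 6 | 20.0% | 46.7% | 56.1% |

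- Position 3: the first two patients share an arm with probability 1/5.
- Position 4: the first three are all in different arms with probability 8/20 = 2/5 (best guess 1/3). Otherwise 0, 1 and 2 places remain (best guess 2/3). So 2/5 × 1/3 + 3/5 × 2/3 = 8/15.
- Position 5: it is certain only if the last two places belong to the same arm, probability 1/5. So 1/5 × 1 + 4/5 × 1/2 = 3/5.

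Over 108/6 = 18 complete blocks, 18 × 1.2 = 21.6 allocations are expected to be certain. Incomplete last blocks would change this slightly.

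**2. Partial knowledge.** The article does not give the number of acupuncturists per centre. Assume k of them, patients split at random, no sharing, and each acupuncturist knowing the position in the sequence.

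- Position 5 is certain with probability (1/k)^4 × 1/5: all four earlier patients were the acupuncturist's own and form two complete pairs.
- Position 6 is certain with probability (1/k)^5 + (1/k)^4 × (1 − 1/k) = (1/k)^4: all five were the acupuncturist's own, or all but the unpaired one.
- Certain share = (6/5)(1/k)^4 ÷ 6 = 0.20/k^4. For k = 1 this is 20%, for k = 2 it is 1.25%, for k = 3 it is 0.25%. Pooling restores 20%.

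**3. Illustration of bias, on an assumed rule.** Suppose prognosis is shifted by +d when OE is the most likely next arm and by −d when it is the least likely, at every opportunity in both centres. Enumerating the 90 orders gives an expected OE−SE difference of 0.45d if OE must be strictly most or least likely, and 0.80d if ties count. For d = 0.25 SD that is 0.11 to 0.20 SD. Simulated t-tests of OE against SE with 36 per arm then reject a true null about 7% to 12% of the time instead of 5%. The article offers no basis for d or for the rule.

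**4. Effect of varying the block size.** The observer is assumed to know the set of sizes but not the current one, with 54 patients per centre (simulation):

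| Block sizes | Certain | Best guess right |
|---|---|---|
| 6 fixed | 20% | 56% |
| 3/6/9 | about 4% | about 55% |
| 6/9/12 | about 2% | about 52% |

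Under the rule in step 3 with d = 0.25 SD, 6/9/12 lowers the bias from 0.11–0.20 SD only to about 0.09–0.16 SD. 3/6/9 gives essentially no reduction.

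**The case against.** A reader might infer that one allocation in five is simply known to the acupuncturists. The article does not support that. It speaks of acupuncturists in the plural, gives no number per centre, and says only that the treating acupuncturist opens the envelope. The 20% is the share for someone with complete knowledge of the block; step 2 shows how fast it falls without sharing. Colleagues in one department working through one numbered envelope series could easily pool what they know, but that too is inference.

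A reader might also infer that the acupuncturists select patients. Nothing says that they recruit, screen or judge eligibility. Recruitment also runs through posters and social media, and the envelope is opened only once an eligible patient is about to be treated. Who screens is a detail that a full protocol commonly holds. This stands as a limit on the point: the route is possible, not shown. It does not remove the point, because opening after enrolment protects the current patient's assignment but not the prediction of the next one, and the stated separation of roles does not cover enrolment.

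Finally, the SD and type I error figures depend on an invented shift, on how ties are handled, and on every opportunity being used. They show a possible order of magnitude and are not an estimate for this trial.

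**Conclusion.** The point holds in a conditional form. The constant block size of 6 is an explicit choice and is now public; it is not a detail left to another document. Given full knowledge of earlier allocations in a centre's block, 20% of allocations are certain, 47% have at least one arm ruled out, and the best guess is right 56% of the time. These figures are exact for complete blocks.

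Whether that knowledge exists in one place, and whether it reaches those who control enrolment, cannot be settled from the article. There is no evidence here that bias has occurred or will occur. This is an avoidable weakness with a cheap remedy. It would be equally wrong to infer that varying the block size makes allocation unpredictable: it removes most of the certainty and little of the guessing advantage.

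**What to change.** For all envelopes not yet used:

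- The independent third party regenerates the list within centre with block sizes varying at random and including larger blocks, for example 6, 9 and 12. Sizes 3, 6 and 9 would not serve.
- The sizes are withheld from the sites and left out of any published amendment until enrolment closes.
- Section 2.4 states that eligibility and baseline WOMAC are completed and signed before the envelope is opened, by staff who neither open envelopes nor treat, and that past allocations are not passed to them. This is the essential half of the change, given how little the best guess falls. If the full protocol already provides for it, one sentence in section 2.4 is enough.

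The cost is a rerun of the SAS list, repacking of unused envelopes, a short amendment, and some staffing discipline at each site. The statistical downside is a slightly larger possible imbalance within a centre: an unfinished block of 12 (4 per arm) can leave two arms up to 4 apart, against 2 with blocks of 6.

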### Blinding

2.5

Participants, outcome assessors, and statisticians will be blinded to group allocation throughout the study. To maintain blinding, the three groups will be referred to as the OE group, SE group, and EA group, respectively. Due to the particularity of acupuncture, acupuncturists will not be blinded. Acupuncture treatments, outcome assessments, and statistical analyses will be conducted independently by different members of the research team.

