#### Opposing needling plus electroacupuncture (OE)

2.6.1

Acupuncture will be administered bilaterally, including both the side with more significant pain and the contralateral side, which presents with mild or no pain. The selected acupoints include, Zusanli (ST36, bilateral), Yanglingquan (GB34, bilateral), Xuehai (SP10, bilateral), Liangqiu (ST34, bilateral), Dubi (ST35, more affected side), Neixiyian (EX-LE4, more affected side), Yinlingquan (SP9, more affected side), and Ashi points (more affected side). Acupoint locations will be determined according to the National Standard of the People’s Republic of China, *Nomenclature and Location of Acupuncture Points* (GB/T 12346–2021). Figure 2 illustrates the anatomical locations of these acupoints.

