#### Sham opposing needling plus electroacupuncture (SE)

2.6.2

Both knees received acupuncture treatments. The acupuncture protocol on the more affected side was identical to that used in the OE group, while four non-acupoint, non-meridian sites on the contralateral calf—distant from the knee and with mild or no pain—were selected for sham opposing needling. The anatomical locations of these sites are illustrated in Figure 3 and detailed in Supplementary File 1 and Table 2.

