**Figure 3 fig3:**
[figure not shown]
Diagram of non-meridian and non-acupoint locations for the SE group. Screenshot from the mobile application ‘Zhiyuan Meridian and Acupoint’ (知源经络穴位) (https://apps.apple.com/app/id1554030035), with local knee acupoints labeled by the authors. Copyright permission for academic use has been obtained.

**Table 2 tab2:** Detailed description of non- meridian and non-acupoint locations.

Non-meridian and non-acupoint	Acupoint localization
1	6 cun superior to the patella, approximately 1 cun (roughly 2 cm) between the Spleen and Stomach meridians
2	4 cun superior to the patella, between the Spleen and Stomach meridians
3	2 cun posterior to Fengshi (GB31), avoiding the Bladder meridian
4	1 cun medial to Chengjin (BL56)

Sham opposing needling will be performed using the Park sham device (35), which features a blunt, retractable needle tip designed to mimic the sensation of skin penetration without actual insertion. Each needle is supported by a circular adhesive base affixed to the skin surface. The structural principle of the Park sham device is illustrated in Figure 4.

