#### Electroacupuncture alone

2.6.3

The more affected side will receive acupuncture treatment following the same needling procedures, acupoint selection, and electroacupuncture protocol as the more affected side in the OE group.

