## Discussion

3

The present study is expected to provide robust evidence regarding the efficacy and safety of combining opposing needling with electroacupuncture for KOA. By testing the hypothesis that this combination may produce additive or synergistic analgesic effects, the trial aims to elucidate the therapeutic value of integrating these two classical acupuncture techniques. A rigorous three-arm parallel-group design will be employed, including an OE group, a SE group, and an EA group. On one hand, this design allows for the evaluation of the additive effect of opposing needling as well as the overall therapeutic benefit of the combined intervention; on the other hand, both the OE and SE groups receive bilateral needling, which helps reduce the risk of unblinding. In addition, the trial incorporates a comprehensive set of outcome measures, enabling a multidimensional assessment of the therapeutic effects of opposing needling plus electroacupuncture. Finally, the study emphasizes standardization and reproducibility of the intervention: all treatments will be administered by uniformly trained acupuncturists, and quality control and monitoring procedures are established to ensure intervention consistency and internal validity of the results.

Nevertheless, certain limitations remain. The follow-up period is limited to 12 weeks, allowing only preliminary evaluation of efficacy and precluding assessment of long-term effects in KOA; future studies should consider extending the follow-up duration. In addition, this is a two-center study with a relatively small sample size. Larger and multicenter RCTs will be required to further validate the generalizability and external applicability of the findings.

Overall, the results of this study are expected to strengthen the clinical evidence for acupuncture-based management of KOA, inform treatment optimization, and provide a foundation for future research on innovative needling techniques in chronic pain management.

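### The group labels OE, SE and EA cannot blind anyone who sees them, and participant blinding is supported only between OE and SE

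*Protocol article*

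**What the plan says.** Section 2.5 (Blinding) makes a general claim: "Participants, outcome assessors, and statisticians will be blinded to group allocation throughout the study". It excepts no arm. The next sentence gives the method: "To maintain blinding, the three groups will be referred to as the OE group, SE group, and EA group, respectively". The section adds that acupuncturists are not blinded and that treatment, assessment and analysis are done by different people.

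Section 2.4 (Randomization) introduces the same letters as short forms of the treatment names: "opposing needling plus electroacupuncture (OE) group, sham opposing needling plus electroacupuncture (SE) group, or electroacupuncture alone (EA) group".

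The intervention sections describe what each participant experiences:

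- OE (section 2.6.1): "Acupuncture will be administered bilaterally, including both the side with more significant pain and the contralateral side".
- SE (section 2.6.2): "Both knees received acupuncture treatments". On the less affected side, "Sham opposing needling will be performed using the Park sham device".
- EA (section 2.6.3): "The more affected side will receive acupuncture treatment following the same needling procedures". Nothing is described for the other leg.

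The Discussion makes a narrower claim than section 2.5. It says that "both the OE and SE groups receive bilateral needling, which helps reduce the risk of unblinding", and it makes no such claim for EA.

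**The concern.** Two statements in section 2.5 do not fit the rest of the document.

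The first is the coding. A blinding code works only if its meaning is unknown to the people it is meant to blind. Here the code is the treatment abbreviation, defined one section earlier and used openly throughout the article.

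The second is the unqualified claim about participants. Whether one leg or both are treated is plain to the patient at each of the 24 sessions (section 2.6.6). The document describes nothing that would hide this difference between EA and the other two arms.

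The primary outcome is the change in WOMAC to week 8, and the secondary outcomes are mostly pain, function and quality-of-life scales. Answers on such scales depend on what the patient believes about the treatment received. If comparisons with EA are reported as participant-blinded, readers will give them more weight than the design supports. For the statistician, some judgement remains after the data are seen. Section 2.12 leaves open whether missingness looks systematic when it is at or below 5%, and which sensitivity analyses to run. Those choices are better made without knowing the arms.

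**Working it through.** The point rests on no sample size, power or event figure, so there is no stated figure to reproduce. The check sets the sections side by side and takes each blinded role in turn.

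**Inputs**

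| Item | Source | Content |
|---|---|---|
| Who is blinded | 2.5 | Participants, assessors, statisticians; no arm excepted |
| Coding measure | 2.5 | Labels OE, SE, EA |
| Meaning of labels | 2.4 | Abbreviations of the three treatments |
| OE needling | 2.6.1 | Both sides, real needles |
| SE needling | 2.6.2 | Real needles on the more affected side; non-penetrating sham device on the other, manipulation matched to OE and withdrawal simulated |
| EA needling | 2.6.3 | More affected side only; no contralateral sham described |
| Staff roles | 2.5 | Treatment, assessment and analysis kept separate |
| Where masking is argued | Discussion | OE and SE only |

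**Statisticians.** They must work with a group variable. If it takes the values OE, SE and EA, as section 2.5 provides, every arm is identified. Keeping the roles separate does not help, because the label itself carries the information. The stated method defeats the stated aim.

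**Assessors.** The label would unblind them if they saw it, but no section says that they do. They are separate from the acupuncturists. They could also learn from the participant which legs were needled, and the article describes no step to prevent this. Their blinding is therefore not secured, but it is not shown to fail.

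**Participants.** Three arms give three pairwise comparisons:

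1. OE versus SE: both sides are treated in both arms, with a sham device and matched handling. Masking is provided for.
2. OE versus EA: two sides against one, with nothing to conceal the difference. Masking is not supported.
3. SE versus EA: the same as for OE versus EA. Masking is not supported.

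The participant-blinding claim is thus supported for one of three comparisons. The unsupported two are those that involve EA, which is planned to hold 36 of the 108 participants (section 2.3).

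**The case against.** The best defence has four parts.

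*The comparison that isolates opposing needling is masked.* This stands. OE versus SE has a described sham procedure. A reader might infer from the labels and the EA arm that the trial has no blinding at all. The documents do not support that reading.

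*Nothing says that assessors see the labels, or that the labels are printed on case report forms.* This also stands, and it limits the point on assessors to inadequate protection. Section 2.9 provides for emergency unblinding, which suggests that some operational masking exists beyond the labels. For the same reason it would be wrong to say that all records are unblinded, since the article does not say which records carry a label.

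*One-sided needling reveals the arm only to a participant who knows that other arms are needled on both sides.* This is fair. The information given to participants is not shown. Participant blinding against EA is therefore not assured, but it is not proven to be absent. An EA arm without a contralateral sham is also a legitimate design choice; only the unqualified claim is wrong.

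*A condensed article leaves coding details to other documents.* This stands for details that are merely absent. It does not rescue a sentence that names treatment abbreviations as the blinding measure.

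Two further inferences are tempting and should not be drawn:

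- The planning means in section 2.3 give SE minus EA = 22.42 − 8.87 = 13.55 points and OE minus EA = 32.3 − 8.87 = 23.43 points. The ratio, 13.55/23.43 = 58%, might be read as the share of the effect due to expectation. The means are planning assumptions from two cited sources that cannot be checked here. A difference between SE and EA could also reflect skin contact, attention or differences between the source studies. The ratio does not measure bias.
- The normality checks in section 2.12 might be taken as a way for an unblinded statistician to influence the efficacy result. They apply only to the baseline comparisons; efficacy is analysed by ANCOVA.

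**Conclusion.** The point holds in two parts. First, the labels in section 2.5 cannot blind a statistician, or anyone else shown them, because section 2.4 defines them as the treatments. This follows from the text alone. Second, the unqualified statement that participants are blinded is supported only for OE versus SE. For OE versus EA and SE versus EA, participant blinding is not assured and patient-reported outcomes may carry expectation bias.

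The second part assumes that no contralateral procedure exists for EA beyond what section 2.6.3 describes. How far EA participants are actually unmasked depends on what they are told about the other arms. For assessors, the conclusion is only that blinding is inadequately secured. The size of any bias cannot be estimated from the document.

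The correction should be in place before anyone meant to be blinded handles labelled data, because blinding cannot be restored afterwards.

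**What to change.** In section 2.5:

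1. Replace OE, SE and EA with neutral codes, for example X, Y and Z, in the analysis dataset and on any form that assessors or statisticians see. The independent third party that generates the sequence (section 2.4) keeps the key until the database is locked and the primary analysis is complete.
2. State that participants are blinded between OE and SE only. Describe OE versus EA and SE versus EA, in the protocol and in the report, as comparisons without assured participant blinding, in which patient-reported outcomes such as WOMAC may carry expectation bias.

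The cost is minor relabelling, a short change of wording and a less favourable blinding claim. No additional participants or procedures are needed, and the three arms stay as they are.

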### Study groups and interventions

2.6

In this trial, acupuncture treatments will be performed by trained and certified acupuncturists with at least 500 h of clinical experience. Only those who have completed the standardized clinical operation training for this study and passed the qualification assessment are eligible to perform acupuncture. The training is conducted in strict accordance with the study’s Standard Operating Procedure (SOP) and includes communication skills, detailed acupuncture operation specifications (needle insertion depth, manipulation techniques, rotation angle and frequency, and Deqi elicitation), and the use of Park sham needles. Upon completion of the training, acupuncturists must pass the assessment and sign a “Declaration of SOP Acknowledgment and Compliance.” During the trial, monitoring staff will perform regular checks to ensure that acupuncture procedures are strictly standardized.

